#### Secondary

Renal function and changes in this defined by:
Plasma creatinine (3 and 12 months)eGFR (12 months)Change in plasma creatinine at 3 and 12 months from the following time-points
○ Highest measured plasma creatinine during the cause of AIN○ Plasma creatinine at time of renal biopsy○ Plasma creatinine at day 0 (inclusion)Number of patients with end stage renal failure and RRT (chronic dialysis or transplantation)For patients in whom a prior, baseline p-creatinine is available, the following will be analyzed
○ Number of patients not on renal replacement therapy who returns to baseline creatinine or lower within 3 and 12 months after inclusion.○ Difference between p-creatinine after 3 and 12 months and baseline.Baseline p-creatinine is defined as the last recorded p-creatinine while the patient’s condition is considered as stable. If more than one such measurement is recorded within the last year, the baseline value is calculated as the average of the last 3 measurements. If more than one measurement is present from the same day an average of these measurements will be included as one of the 3 last measurements.In the prednisolone treated group the importance of “treatment delay” is analyzed by examining eGFR at 3 and 12 months. This will be explored using three different definitions of treatment delay:
○ Days from first symptom to inclusion in this project and initiation of prednisolone○ Days from first contact to the Danish health care system to inclusion in this project○ Days from first contact to a nephrology department to inclusion in this projectQuality of life estimated by a questionnaire (SF 36) at and 12 months

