### Hypotheses

This study will examine the following hypotheses:
Prednisolone treatment in AIN is associated with a higher eGFR 3 and 12 months after inclusion when compared to no prednisolone treatment.Prednisolone treatment in AIN is associated with a greater decline in plasma creatinine from inclusion to 3 and 12 months after when compared to no prednisolone treatment.Prednisolone treatment in AIN shortens the time to remission or partial remission when compared to no prednisolone treatment.Prednisolone treatment in AIN reduces the number of patients requiring renal replacement therapy when compared to no prednisolone treatment.A greater timespan from the presentation of AIN to the initiation of prednisolone treatment is associated with a lower eGFR 3 and 12 months after inclusion.

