### Study overview

Overview of the study from inclusion to week 52 is shown in Table 1.

**Table 1 Tab1:** Overview of the study from inclusion to week 52

		Day 0^a^	Day 2	Day 4	Week 1	Week 2	Week 4	Week 8	Week 12	Week 26	Week 52
Treatment	A	No treatment									
	B	Oral prednisolone tapered over 8 weeks									
Medical history		+									
Biochemistry A		+	+	+	+	+	+	+	+	+	+
Biochemistry B		+							+	+	+
Biochemistry C		+			+		+		+		+
Study medication (group B)		+			+	+	+	+			
Blood pressure, HR		+	+	+	+	+	+	+	+	+	+
Clinical examination		+			+	+	+	+	+	+	+
24 h urine		+					+		+		+
Spot urine A		+	+	+	+	+	+	+	+	+	+
Spot urine B		+			+		+		+		+
Questionnaire (SF36)		+					+		+		+

Biochemistry A: P-sodium, p-potassium, p-total calcium, p-ionized calcium, p-phosphate, p-creatinine, eGFR, p-urea, p-glucose, WBC, p-c-reactive protein (CRP), b-sedimentation rate, p-PTH

Biochemistry B: Hemoglobin A1C. p-TSH, p-25-Hydroxy-Vitamine D2 + D3

Biochemistry C: TGF-β1, BMP-7

Study medication: Dose and adverse effects

Clinical examination: Body weight and physical examination

24-h urine collection: Urinary volume and urinary sodium, creatinine, and albumin excretion

Spot urine A: Urine-dip stick (hemoglobin, protein, leucocytes, glucose, nitrite), urinary albumin and creatinine concentrations and urinary albumin/creatinine ratio

Spot urine B: Urinary concentration and ratios in relation to urinary creatinine of TGF-β1, BMP-7, A1M, B2M, MCP-1, NGAL, NAG, IL-18, TIMP-2, KIM-1, IGFBP7 and CD163-

Questionnaire: SF36 is filled in by the patient

^a^Before start of study medication

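### Change from the highest creatinine allows a reference value reached after randomisation, so preventing further worsening counts as a smaller improvement

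*Protocol article*

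**What the plan says.** Under Endpoints, Secondary, the protocol article lists "Change in plasma creatinine at 3 and 12 months from the following time-points" and names three reference values:

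- "Highest measured plasma creatinine during the cause of AIN" (the word before AIN is evidently meant as course);
- "Plasma creatinine at time of renal biopsy";
- the value on day 0, at inclusion.

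The second and third are each tied to a moment before treatment. The first has no end date, and nothing elsewhere in the article confines it to values taken before randomisation.

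Table 1 (Study overview) puts creatinine in Biochemistry A. That panel is drawn on day 0, which the footnote places "Before start of study medication", and again on days 2 and 4 and at weeks 1, 2, 4, 8, 12, 26 and 52.

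The corresponding hypothesis (Hypotheses section) is anchored differently. It expects a "greater decline in plasma creatinine from inclusion to 3 and 12 months after", that is, a fall measured from inclusion and not from the peak.

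**The concern.** A change score compares randomised arms fairly only if its starting value is fixed before treatment can act on it. Here the starting value is a maximum that may be reached while one arm is on prednisolone and the other is not. The inclusion criteria ask for creatinine above a threshold or a rise from baseline. They do not ask that it has stabilised or begun to fall, so patients may enter while still getting worse.

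Take a control patient who worsens after day 0 and then recovers, and a treated patient who never worsens and ends at the same 3-month creatinine. The control patient is credited with the larger fall. An early benefit, which the trial is designed to find, is thus scored against the treatment, and the result can contradict both the primary endpoint and the stated hypothesis. The same peak is the reference at 12 months, so the distortion carries over to that time point.

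**Working it through.** **The plan's own figures.** The article gives no number for this endpoint. Its sample size for the primary endpoint (difference 10, SD 18, power 0.80, two-sided 5% assumed) reproduces as 51 per group and does not bear on this point.

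**Formula.** Let A be control and B prednisolone. Let m be mean creatinine at 3 months and P the mean highest value. Fall from peak is P − m, so

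B minus A = (P_B − m_B) − (P_A − m_A) = (m_A − m_B) − (P_A − P_B).

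The first bracket is the true benefit at 3 months. Randomisation makes the pre-randomisation peak equal in expectation between arms. P_A − P_B is therefore the between-arm difference in mean rise *above the pre-randomisation peak*, and that difference is the bias. It equals the difference in rise above day 0 only where day 0 was the highest value so far.

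The article gives no creatinine trajectories, so every input below is an assumption. Units are µmol/L, and a positive difference favours prednisolone.

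**1. No true difference at 3 months, day 0 the highest value so far.** Suppose 30% of controls and 10% of treated patients rise further and then recover.

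- Rise of 100: bias = (0.30 − 0.10) × 100 = 20 against prednisolone.
- Rise of 150: bias = (0.30 − 0.10) × 150 = 30 against prednisolone.
- Change from day 0: difference 0 in both cases.

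**2. A true benefit of 20.** Day 0 is 300 in both arms, the treated peak is 300, and 3-month values are 160 (control) and 140 (treated).

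| Control peak | Fall from peak, control | Fall from peak, treated | Difference from peak | Difference from day 0 |
|---|---|---|---|---|
| 300 | 140 | 160 | +20 | +20 |
| 310 | 150 | 160 | +10 | +20 |
| 350 | 190 | 160 | −30 | +20 |
| 400 | 240 | 160 | −80 | +20 |

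The sign reverses once the control peak exceeds the treated peak by more than the true benefit of 20.

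**3. A mixed population.** This simulation used 200,000 patients per scenario. The pre-randomisation peak had median 320, and day 0 was 85% to 100% of that peak. A fraction of patients was still rising after day 0, by 120 on average, and treatment removed half or all of that rise. The entries are the mean difference in fall from peak.

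| Still rising | Share of rise removed | True benefit 0 | True benefit 20 |
|---|---|---|---|
| 10% | half | −5.7 | +14.3 |
| 10% | all | −9.9 | +10.1 |
| 30% | half | −17.0 | +2.8 |
| 30% | all | −29.3 | −9.7 |
| 50% | half | −28.7 | −8.5 |
| 50% | all | −49.0 | −29.0 |

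A reference fixed on or before day 0 returns the true benefit, 0 or 20, in every row. The 30%/all row also shows why the pre-randomisation peak matters: 0.30 × 120 = 36 is the mean rise above day 0, but the bias is 29.3, because part of that rise only regains a level already reached.

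**The case against.** The strongest reply concerns reach. This is one of three reference values for one secondary endpoint. The biopsy and day 0 versions precede study medication. Absolute creatinine at 3 and 12 months and eGFR at 12 months need no reference value. The primary endpoint is untouched, and the only hypothesis about creatinine change is anchored at inclusion. The sound comparison is therefore already in the plan, and a discrepant peak result would sit beside it. That limits the harm but does not make this version valid, and three versions that may disagree are harder to interpret.

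A second reply is that the wording is loose rather than wrong: it could mean the peak at presentation, and an analysis plan that is not shown might set the window. But the biopsy and day 0 values are named separately, and a peak over the episode with no end date naturally takes in the scheduled values after day 0. As written, the rule allows a reference affected by treatment.

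A third reply is that the size rests on invented trajectories, and that the example with equal 3-month values shows a spurious difference, not a reversal. Both statements are correct. The size is illustrative only. Reversal appears in the second example and in three of the six simulated rows with a true benefit of 20; in the other three the benefit is only reduced.

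**Conclusion.** The concern holds. The stated rule lets the reference value be reached after randomisation, and the direction of the bias follows from arithmetic: if treatment prevents further worsening, the endpoint understates its benefit by exactly the amount by which it lowers the mean peak above the pre-randomisation level. Under the assumptions shown, that is 20 to 30 µmol/L in the simple case and about 6 to 49 µmol/L across the simulated scenarios, enough in some of them to reverse the sign of a true benefit of 20 µmol/L. How often creatinine peaks after day 0 cannot be learned from the article, and if it never does, the bias is nil. Confidence is high for the mechanism and low for the size. The point should be corrected, but it is confined to one version of one secondary endpoint.

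**What to change.** Define the reference as the highest plasma creatinine recorded on or before day 0, before randomisation. That removes the bias and brings the endpoint into line with the hypothesis, which measures the fall from inclusion. If a peak after randomisation is of interest, report it as an outcome in its own right, not as a starting value.

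The pre-randomisation peak can also be used as a covariate. This is optional, because limiting the window already cures the defect. With that peak as a linear covariate, change from peak and absolute creatinine give the same treatment estimate, so the adjusted version would add nothing to the creatinine endpoint already listed, analysed with the same covariate.

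The cost is one phrase in the endpoint definition, with no new data and no effect on the sample size. The Time schedule section reports 30 of the planned 110 patients included at the time of writing. The change should be made, and dated, before outcome data are compared by arm.

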**Methods:**

The study is a randomized, controlled, prospective, open label multicenter study, including incident adult patients with biopsy proven AIN. Patients will be randomized 1:1 to one of 2 treatment regimens:
A.No prednisolone treatment (control group) andB.B) Oral prednisolone treatment staring with 60 mg daily tapered over 8 weeks.

One hundred ten patients (55 in each group) are planned to be included and followed for 1 year. Primary outcome is renal function estimated by eGFR 3 months after inclusion. Secondary outcomes are renal function after 12 months and need for renal replacement therapy and quality of life after 3 and 12 months. In addition, with-in prednisolone group analysis are performed to estimate the importance of treatment delay. Exploratory analyses include analysis of biomarkers in urine and plasma and the evaluation of these biomarkers in relation to renal prognosis and re-evaluation of renal biopsies to identify possible renal prognostic factors.

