## Background

Acute renal failure is associated with greatly increased mortality and morbidity irrespective of its cause [1, 2]. Acute interstitial nephritis (AIN) is an important and common cause of acute renal failure and occurs in 13–27% of renal biopsies performed in acute renal failure requiring dialysis in 40% of cases [3–6]. Histologically AIN is characterized by peritubular inflammation while glomeruli and vessels are typically spared [7]. Although some patients recover renal function completely, as many as 30–70% do not fully regain renal function leading to chronic kidney disease (CKD) [6, 8–14]. CKD is associated with increased morbidity and mortality. Two recent studies suggested that the risk of end stage renal disease requiring dialysis after biopsy proven AIN is 5–7% [6, 13].

In addition to renal failure AIN may present with joint pain (45%), fever (36%), skin rash (22%), eosinophilia (35%), microscopic hematuria (67%), macroscopic hematuria (5%), leukocyturia (82%), non-nephrotic proteinuria (93%), nephrotic proteinuria (3%) and nephrotic syndrome (1%) [15]. AIN can be subdivided in 3 categories based on the precipitating cause: drug induced (75%), infection (5–10%) or autoimmune diseases (15–20%) [5, 7, 16–18]. The pathophysiological mechanisms leading to renal inflammation in AIN are not fully clarified. Fibrotic changes can be observed 7–10 days after the beginning of the inflammatory process and if the triggering cause is not eliminated, the inflammation may proceed to interstitial fibrosis, tubular atrophy and chronic renal failure [19]. Studies have shown that macrophages, lymphocytes and activated tubular cells produce various cytokines that stimulate proliferation of fibroblast cells leading to fibrosis [20, 21]. Transforming growth factor-β1 (TGF-β1) promotes fibroblast activity in vitro and alters the phenotype of mesangial cells to a more fibroblast-like phenotype [22, 23]. Transgenetic mice overesxpressing TGF-β1 show increased renal fibrosis [24, 25]. Thus, TGF-β1 appears to play a central role in the development of renal fibrosis [26]. Bone morphogenetic protein-7 (BMP-7), on the other hand is a natural antagonist of TGF-β1 with anti-fibrotic and anti-inflammatory properties [26]. The roles of TGF-β1 and BMP-7 in AIN; however, have not been elucidated.

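### The treatment-delay analysis uses the prednisolone arm only, so it can show a prognostic association with delay but not the importance of delaying treatment

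*Protocol article*

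**What the plan says.** The last of the five statements under Hypotheses reads: "A greater timespan from the presentation of AIN to the initiation of prednisolone treatment is associated with a lower eGFR 3 and 12 months after" inclusion. The analysis is placed under Endpoints, Secondary, where the importance of delay, for the prednisolone group alone, "is analyzed by examining eGFR at 3 and 12 months". The Methods part of the abstract confirms the population: "with-in prednisolone group analysis are performed to estimate the importance of treatment delay".

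Three definitions of delay are listed. The first is "Days from first symptom to inclusion in this project and initiation of prednisolone". The second is "Days from first contact to the Danish health care system to inclusion in this project". The third runs from first contact with a nephrology department to inclusion. All three end at inclusion, and only the first mentions prednisolone.

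The Statistics section offers a general linear model for factors affecting the primary endpoint, and confounder adjustment for correlations between the primary endpoint and other outcomes. Neither sentence names delay or brings the controls into the delay question.

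**The concern.** The label given to the analysis concerns the timing of therapy, but the population chosen can only describe how patients who entered late fared on prednisolone. Such patients may do worse because their disease has run longer, because prednisolone works less well when started late, or both.

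The Background gives a reason to take the first explanation seriously: "Fibrotic changes can be observed 7–10 days after the beginning of the inflammatory process". It adds that inflammation may go on to fibrosis and chronic failure if the trigger persists. That mechanism does not depend on prednisolone.

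At stake is how a negative slope is read. It could be taken as evidence for early prednisolone when it shows only that late presentation carries a worse prognosis. The trial has concurrent untreated controls who could help tell these apart, and the stated analysis leaves them out.

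**Working it through.** **The article's own figure.** No sample size is stated for the delay analysis. The primary calculation (difference 10, SD 18, power 0.80, significance level 0.05, taken as two-sided) gives n = 2 × (1.960 + 0.842)² × 18² / 10² = 50.9, so 51 per group, as stated. An exact t-test gives 52, which is close enough. Going from 51 to 55 allows for 1 − 51/55 = 7.3% dropout. The sample size is not in dispute.

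**What each analysis estimates.** Let T = 1 for prednisolone and 0 for control, and let D be delay to inclusion:

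eGFR = b0 + b1·T + b2·D + b3·T·D + error

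- Slope on D among controls: b2, the prognostic part.
- Slope on D in the prednisolone arm: b2 + b3.
- Change in the prednisolone effect per unit of delay: b3.

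The planned analysis estimates b2 + b3. With T = 1 for everyone in it, no covariate can split the sum. The controls supply b2, and the difference between the two slopes is b3.

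**How often the one-arm test is significant when b3 = 0.** The article gives no distribution of delay and no correlation with eGFR, so the strengths below are assumptions chosen to show a range.

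| Set-up | Assumed prognostic strength | One-arm test significant | Interaction significant |
|---|---|---|---|
| 55 per arm, no drug effect, outcome SD 18, delay SD 20 days, 3,000 runs | correlation −0.2 / −0.3 / −0.4 | 29% / 61% / 85% | 4.5% / 4.6% / 4.4% |
| 51 per arm, constant benefit of 10 ml/min, residual SD 18, 20,000 runs | −2.5 / −5 / −7.5 ml/min per SD of delay | 16% / 48% / 81% | 5.2% / 5.2% / 5.0% |

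The two set-ups cover similar strengths. In the second, the correlations are −2.5/√(2.5² + 18²) = −0.14, −5/√(5² + 18²) = −0.27 and −7.5/√(7.5² + 18²) = −0.38. With a slope of zero, the one-arm test rejects in 4.8% and the interaction in 5.0%, as they should.

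**Precision.** With delay scaled to SD 1 and residual SD 18, the detectable value at 80% power is 2.802 × SE.

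- 51 per arm, one-arm slope: SE = 18/√51 = 2.52, detectable 7.1 ml/min per SD.
- 51 per arm, interaction: SE = 18 × √(2/51) = 3.56, detectable 10.0 ml/min per SD.
- 55 per arm: detectable 6.8 for the slope and 9.6 for the interaction.

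**Can the intervals be computed for controls?** All three end at inclusion, so yes. Definition 1 needs its endpoint stated as inclusion for patients who receive no prednisolone. Table 1 lists medical history at day 0 without restricting it to group B, whereas it does restrict study medication to that group.

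**The case against.** The hypothesis is worded as an association, and one arm can estimate an association. The article presents the delay analysis as something to be explored, and it is secondary. Model detail may sit in a fuller plan. All of this stands and limits the weight of the point. It does not settle the matter, because the article itself fixes the analysis population, in two places, and describes the result as the importance of treatment delay.

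Four stronger readings are tempting, and the article does not support them.

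- A reader might take the 16% to 85% as false-positive rates. They are the power to detect an association that was built into the simulations, so they are not errors for the hypothesis as worded. They become errors only if the slope is read as an effect of treatment timing.
- A reader might infer that the trial could recommend early prednisolone even if the drug did nothing. The randomized intention-to-treat comparison is primary. With an inert drug it would normally be null and would frame any secondary slope.
- A reader might say the plan repeats a weakness that it criticizes elsewhere. The Background and Discussion fault retrospective studies for selection bias. The Background reports an earlier association between delay and outcome in treated patients without criticizing it on this ground.
- A reader might take the Background to say that longer disease predicts lower eGFR regardless of treatment. It says only that fibrotic changes can be seen at that stage and may progress if the trigger remains. That delay is prognostic is a plausible inference, most direct for the first-symptom definition.

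The interaction is also weak here. At 51 per arm its detectable size per SD of delay is about the whole 10 ml/min effect that the trial is designed to find, and there are three definitions and two time points. This is a good reason not to present it as a powered test, but it does not make the one-arm slope answer the timing question.

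**Conclusion.** The point holds as a limit on interpretation and as an omitted comparison. The planned one-arm slope is a valid prognostic association. It does not identify how much prednisolone benefit is lost with delay, because b2 and b3 enter only as a sum. This conclusion is algebraic and needs no assumed numbers, beyond prednisolone starting at inclusion as the schedule provides.

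The size of the problem in this trial is unknown. The range of 16% to 85% depends on assumed correlations of about −0.14 to −0.4, for which the article gives no basis. The result of about 5% for the interaction assumes that the prognostic slope is the same in both arms.

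The interaction has a limit of its own. Randomization protects the arm comparison at any given delay, but delay itself is not randomized. The interaction therefore shows whether the benefit varies with delay, not that delay alone causes the variation.

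The primary analysis and the sample size are unaffected.

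**What to change.** 1. Compute each of the three intervals to inclusion in both arms, ending definition 1 at inclusion for controls.
2. For eGFR at 3 and at 12 months, fit arm, delay and arm-by-delay in all randomized patients.
3. Base any statement about treatment timing on the interaction, reported as an estimate with a confidence interval. State that it is not a powered test.
4. Keep the within-arm slope and label it a prognostic association.

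The cost is analysis wording, plus the same symptom and contact dates for controls wherever these are not already entered. When the article was written, 30 of the planned 110 patients had been included, so most could be covered prospectively. The downside is precision: with 51 per arm the standard error rises from 2.52 to 3.56 ml/min per SD of delay, and the result will probably be inconclusive. If the sponsor does not want the interaction, the minimum change is to call the one-arm result prognostic and make no claim about the timing of treatment.
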